### Trial sample size

The primary outcomes of this trial include changes in pain (NRS) and physical function (WOMAC) over 6 months and the intervention will be considered beneficial if it changes either one or both of the primary outcomes. A Cochrane Review shows that exercise has a moderate effect size for pain and function in knee OA [10]. Calculations thus assume an effect size between the least-performing treatment group (presumed to be the *Exercise* group) and the control group of 0.4. Given that the effect size between two treatments will be less than between treatment and control, we assumed an effect size of 0.3 between the *Exercise* group and the *Exercise plus weight management* group. We chose 0.3 because any smaller effect is unlikely to be clinically relevant or cost-effective to implement in real-world settings given the considerable expense of the weight management program relative to the exercise components of this combined intervention. Calculations also assume a correlation between baseline and follow-up measurements of 0.4, power 80, 15% loss to follow-up (based on our previous research [71, 72]), and two-sided significance level of 0.05. Based on these calculations we require 173 participants in each treatment group, and 69 participants in the control group arm, giving a total sample size of 415 participants.

There are different levels of clustering for each of the three groups; in the *Exercise* group, participants are clustered by physiotherapist, in the *Exercise plus weight management* group, people are clustered by physiotherapist and dietitian, and in the control group, there is no clustering. Given the geographical and demographic spread of participants, we expect that the intra-cluster correlation of outcomes treated by the same dietitian or physiotherapist to be of the order of 0.01. Modifying the formulae [73] to allow for correlations between baseline and follow-up measurements, and assuming that there are five dietitians delivering the *Exercise plus weight management* treatment, the effect size that can be detected between the *Exercise* and the *Exercise plus weight management* groups with 80% power given the originally calculated sample size increases slightly to 0.32.

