### Analysis

We will use intention-to-treat analyses, using multiple imputation to account for missing data and details on the imputation will be reported [74]. Participants will be included in their randomised treatment groups regardless of their post-randomisation behaviour. *P* values less than 0.05 will be considered significant. Outcomes (primary, secondary, and determinants) will be compared between groups as follows: i) *Exercise* vs *Exercise plus weight management*; ii) *Exercise* vs control, and; iii) *Exercise plus weight management* vs control. For continuous data, mean differences in change over time between these groups will be estimated using linear regression models fit to data from both follow-up time points, with random effects for participants, and accounting for clustering by physiotherapist and dietitian in the *Exercise* and *Exercise plus weight management* groups. Models will be adjusted for the stratification variable (history of knee surgery) and values of the outcome at baseline. Terms for time and treatment will be included, with an interaction between the two. Regression assumptions will be assessed using standard diagnostic plots. For binary outcomes, logistic regression models will be fit using generalised estimating equations to account for clustering, with risk differences and 95% confidence intervals calculated. This will include a comparison of the proportion of participants in each group whose improvement meets or exceeds the minimal clinically important difference for each of the primary outcomes. For ordinal outcomes, proportional odds models will be fit similarly. Multinominal models will be applied if the assumption of proportional odds is not valid. To assess the sensitivity of the results for the primary outcomes in situations in which the outcomes are missing not at random, we will apply a pattern-mixture approach that involves fitting regression models that adjust for departures from the missing at random assumption [75].

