Economic evaluations will assess and compare the cost-effectiveness of the interventions. This will involve analysis of: i) cost per extra person with a clinically significant improvement in pain (measured as 1.8 point reduction on the pain score) and function (6 unadjusted WOMAC units), and; ii) per quality-adjusted life years (QALYs) gained for the intervention compared to control at 12 months. QALYs will be calculated based on utility scores using the AQoL-8D at baseline and 12 months. The difference in health care usage and productivity lost between baseline and 12 months will be compared for intervention and control groups. The association between utility gains on the AQoL-8D and productivity will also be compared between the intervention and control groups.

To evaluate the longer-term effects of the *Exercise* and *Exercise plus weight management* interventions on total knee joint replacement and knee arthroscopy surgical rates, logistic regression models for surgery will be fit using generalised estimating equations to account for clustering by physiotherapist and dietitian, with treatment effects summarised using risk differences and 95% confidence intervals. The stratifying variable of history of knee surgery will be adjusted for.

To evaluate whether there is a relationship between amount of weight loss and changes in pain and/or function, linear regression models for changes in pain and outcome will be fit and will include a term for weight lost at 6 and 12 months (as percentage of baseline weight), adjusting for baseline level of the outcome, assigned treatment group, and stratifying variables. Demographic variables thought to affect both weight loss and outcomes levels, including age and sex, will also be included in the model. Fractional polynomial terms for weight lost will be assessed to investigate if the relationship between outcomes and weight loss is non-linear. Standard diagnostic plots will be used to assess regression assumptions. We will also evaluate whether there is a relationship between adherence to exercise and changes in pain and/or function by estimating a complier-average causal effect using a two-stage least squares approach [76].

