Finally, we will conduct exploratory analyses to investigate whether the relative effects of each intervention on change in each of the primary outcomes is moderated by: i) expectation of treatment effects; ii) sex; iii) pain self-efficacy; iv) BMI; v) employment situation; vi) history of knee surgery (contralateral total knee joint replacement surgery and/or knee arthroscopic surgery); vii) self-efficacy for eating control, and; viii) depression. These moderators were selected based on previous research and/or theoretical plausibility (Table 5). Models will include terms for treatment, the moderator variables, and an interaction between the two. Fractional polynomials will be included for the continuous moderators [88]. The estimated effects of treatment and 95% confidence intervals will be presented for each moderator, with visual representations included for continuous moderators.

**Table 5 Tab5:** Overview of selected demographic and clinical moderators

Selected moderator variables	Justification		
Expectation of treatment effects	Based on evidence that greater treatment expectations are associated with more favourable outcomes in people with osteoarthritis [77–79]. *Hypothesis*: Participants in the intervention groups who have greater treatment expectations will report greater improvement in primary outcomes than those who have lower treatment expectations (relative to control group).		
Sex	Based on evidence that being male is associated with better outcomes in pain and physical function after supervised strengthening exercises [80] and evidence from a review that being female is associated with greater weight loss intentions [81]. *Hypothesis*: Participants in the intervention groups who are male will report greater improvement in primary outcomes than those who are female (relative to control). Participants in the *Exercise plus weight management* group who are female will report greater improvement in primary outcomes than those who are male (relative to *Exercise* group).		

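### The exploratory moderator models are listed without the baseline and stratification adjustment of the primary model; carrying it over is a minor, free gain in precision

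*Protocol article*

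**What the plan says.** The last paragraph of the Analysis section plans "exploratory analyses to investigate whether the relative effects of each intervention on change in each of the primary outcomes is moderated by" eight baseline characteristics, one of which is history of knee surgery. It then gives the model: "Models will include terms for treatment, the moderator variables, and an interaction between the two". It adds fractional polynomials for continuous moderators. It names neither the baseline value of the outcome nor the stratification factor, and it does not refer back to the primary model.

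The other models in the same section do name their adjustment:

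- Primary model for continuous outcomes: "Models will be adjusted for the stratification variable (history of knee surgery) and values of the outcome at baseline".
- Models relating weight loss to change in pain and function: "adjusting for baseline level of the outcome, assigned treatment group, and stratifying variables".
- Models for longer-term surgical rates: "The stratifying variable of history of knee surgery will be adjusted for".

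The Trial sample size section supplies the correlation needed to put a size on the difference: "Calculations also assume a correlation between baseline and follow-up measurements of 0.4".

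**The concern.** Three sets of models in the section state their adjustment, and the moderator paragraph, which also goes into model form, does not. An analyst who took its list literally would regress raw change on treatment, moderator and interaction. At a baseline to follow-up correlation of 0.4, a raw change score is noisier than the follow-up score itself, whereas adjusting for baseline makes the comparison more precise.

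Interaction estimates are imprecise in any trial sized for main effects. Here many of the stated moderator hypotheses (Table 5) are set against the control arm, the smallest of the three. The Discussion expects these analyses to show which patients respond and to help providers target the services. At stake are wider intervals than necessary for those subgroup estimates, and a choice of covariates that the protocol leaves open.

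**Working it through.** **Inputs.** From Trial sample size: correlation ρ = 0.4, effect sizes 0.3 (between the two treatments) and 0.4 (Exercise against control), power 80%, two-sided 0.05, 15% loss, and 173, 173 and 69 participants. From the randomisation section: allocation 5:5:2. Assumed, because the protocol gives no figure: equal baseline and follow-up SDs unless stated, a binary moderator with prevalence p, and interaction sizes in SD units. Clustering and the second follow-up time are ignored throughout.

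**1. The plan's own sample size.** With baseline adjustment the residual variance is 1 − ρ² = 1 − 0.16 = 0.84 (SD = 1).

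- Between treatments: n = 2 × (1.960 + 0.842)² × 0.84 / 0.3² = 146.5, so 147 per arm; 147/0.85 = 172.9, so 173.
- Exercise against control at 2.5:1: n = (1 + 1/2.5) × (1.960 + 0.842)² × 0.84 / 0.4² = 57.7, so 58 controls; 58/0.85 = 68.2, so 69.
- Total: 173 + 173 + 69 = 415, as stated.

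With unadjusted change the variance is 2(1 − ρ) = 1.20, and the first comparison would need 210 completers, or 248 randomised, per arm. The trial was therefore sized on baseline adjustment.

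**2. Variance ratio, unadjusted change to baseline-adjusted.** 2(1 − ρ)/(1 − ρ²) = 2/(1 + ρ).

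| ρ | Ratio (equal SDs) |
|---|---|
| 0.3 | 1.54 |
| 0.4 | 1.20/0.84 = 1.43 |
| 0.5 | 1.33 |
| 0.6 | 1.25 |

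If the baseline SD is k times the follow-up SD, the ratio at ρ = 0.4 is (1 + k² − 0.8k)/0.84. For k = 0.8 this is 1.00/0.84 = 1.19; for k = 0.7 it is 0.93/0.84 = 1.11. Values of k below 1 are possible for pain, because entry requires a score of at least 4 on the 0 to 10 scale.

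**3. Interaction standard error.** SE = √[v(1/n₁ + 1/n₂)/(p(1 − p))], with v = 0.84 or 1.20. At p = 0.5:

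- Between treatments (147 and 147 completers): 0.214 adjusted, 0.256 unadjusted.
- Exercise against control (147 and 59): 0.283 adjusted, 0.338 unadjusted.

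**4. Interaction power** (normal approximation, p = 0.5, equal SDs, ρ = 0.4):

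| Comparison | Interaction (SD) | Adjusted | Unadjusted | Loss (points) |
|---|---|---|---|---|
| Between treatments | 0.2 | 15.3% | 12.0% | 3.3 |
| | 0.3 | 28.9% | 21.6% | 7.3 |
| | 0.4 | 46.5% | 34.7% | 11.8 |
| | 0.6 | 80.1% | 65.1% | 15.0 |
| Exercise vs control | 0.2 | 10.5% | 8.6% | 1.9 |
| | 0.4 | 29.2% | 21.8% | 7.4 |
| | 0.8 | 80.7% | 65.7% | 15.0 |

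Over interactions of 0.2 to 0.8 SD and prevalences of 30% to 50%, the loss runs from 1.7 to 15.4 points.

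**5. Effect of a narrower baseline SD.** For the 0.4 SD interaction between treatments, v = 1.00 (k = 0.8) gives SE 0.233 and power Φ(0.4/0.233 − 1.96) = 40%. With v = 0.93 (k = 0.7), SE is 0.225 and power 43%. The loss against 46.5% is then about 6 or 4 points instead of 11.8.

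**The case against.** The strongest reply is that the sentence does not exclude anything. To say that models will include certain terms is not to say that they contain nothing else. The primary-model paragraph uses similar wording for time, treatment and their interaction after stating the covariates separately, and nobody would read that as removing the covariates. The moderator paragraph itself goes on to add fractional polynomials. Taken as complete, its list would also drop time, participant effects and clustering, which is unlikely to be meant. Nor does the word change imply a raw change score: the baseline-adjusted primary analysis is described in the same way ("mean differences in change over time between these groups will be estimated using linear regression models fit to data from both follow-up time points"). An analysis plan that is not shown may well settle the covariates. All of this stands. A reader might infer that the protocol drops the adjustment, but the text does not say so. What remains is that this paragraph alone gives a term list without the adjustment that the section states for its other models, and does not point back to it.

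Three further inferences are tempting and also fail:

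- **Spurious moderation.** Moderators such as self-efficacy or depression may correlate with baseline pain, so an unadjusted model might seem to produce false moderation through regression to the mean. Randomisation keeps the interaction estimate unbiased. Chance imbalance is sampling error, already counted in the standard error.
- **Conflict with the primary result.** Under randomisation the adjusted and unadjusted models target the same average effect.
- **Loss from the stratification factor.** None of the computed variance ratio comes from it, and the model for history of knee surgery as a moderator already contains it.

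The analyses are also labelled exploratory, and no sample size or primary result depends on them.

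**Conclusion.** The point holds as a minor improvement in precision and consistency. Read literally, the moderator paragraph describes models without the baseline adjustment on which the trial was sized. Fitted that way, their residual variance would be about 1.43 times the adjusted variance at ρ = 0.4 with equal SDs, 1.54 at 0.3 and 1.25 at 0.6. It would be only about 1.1 to 1.2 at ρ = 0.4 if the baseline pain SD is 0.7 to 0.8 of the follow-up SD. The cost in interaction power is roughly 2 to 15 points at equal SDs. No single figure, or narrower band, can be taken from the documents, because they give neither interaction sizes nor moderator splits; the calculation also treats moderators as binary when several are continuous. The 1.43 is conditional on there being no baseline term at all, and should not be read as an established inflation. Bias is not at issue, and the primary conclusions are unaffected.

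**What to change.** Replace the sentence listing the moderator terms with a statement that each moderator model is the primary model for continuous outcomes (baseline value of the outcome, history of knee surgery, time, participant random effects and clustering by clinician) with the moderator and its interaction with treatment added. If an analysis plan already says this, a cross-reference is enough. The cost is one sentence. The baseline values are already collected, so no participants, data or procedures are added.

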### Ethics

Ethical approval has been obtained from the University of Melbourne Human Research Ethics Committee (HREC No. 1750443). All participants will provide written informed consent. The funding agency (Medibank) will be responsible for marketing the study to support recruitment, by making the study known (via email, letters, articles, newsletters and social media) to potentially eligible members. All marketing material viewed by member will include a statement that their involvement in the study will not affect their relationship or policy with Medibank. Medibank will not be involved in statistical analysis.

## Discussion

With the rapidly rising burden of knee OA, there is an urgent need for interventions that improve outcomes and that are also widely accessible to people in rural, regional, and metropolitan communities [89]. Although the effectiveness of exercise therapy on pain and function is well-established, there is relatively limited robust evidence about the additional benefits of weight loss in people with knee OA [4].

This trial will be the first to investigate the clinical- and cost-effectiveness of a remotely delivered service combining dietary weight management and exercise, compared to a service involving exercise only and to an online information-only control group. Such a service has the potential to be a low-cost and accessible way in which people with OA can receive care, thus potentially increasing uptake of recommended management methods, like weight loss and exercise. Findings from this study will inform healthcare providers about the effects of incorporating weight loss components into exercise interventions. Moderator analyses using data from this study will also allow us to determine whether specific sub-groups of participants are more likely to respond to these remotely delivered services, which will allow health service providers to better target interventions to those that would benefit most. Qualitative explorations will provide insight into the feasibility and viability of implementing similar weight management programs into private and public healthcare settings from the perspective of both the participants receiving care, as well as the clinicians involved in delivering it.

A potential limitation of this trial is the targeted sample of participants, including only those who are Medibank Private members with a level of membership that includes arthroplasty surgery. This may potentially limit the generalisability of our findings, however, Medibank Private is one is one of the largest providers of private health insurance in Australia, and participants will be recruited Australia-wide to attempt to maximise the generalisability of the cohort.

## Data Availability

The datasets used and/or analysed during the current study will be available from the corresponding author ([contact]) on reasonable request once the study has been completed.

## Abbreviations

BMI: Body mass index
CSIRO: Commonwealth Scientific and Industrial Research Organisation
MITI: Motivational Interviewing Treatment Integrity tool
NRS: Numeric rating scale
NSAIDS: Non-steroidal anti-inflammatory drugs
OA: Osteoarthritis
RCT: Randomised controlled trial
RPE: Rating of perceived exertion
VLCD: Very low calorie diet
WOMAC: Western Ontario and McMaster Universities Osteoarthritis Index
